#### Withdrawal criteria and management

2.2.4

Patients will be required to withdraw for the following reasons.Patients’s condition worsens, requiring discontinuation of the trial.Serious complications, allergic reactions, significant physiological changes that occur during the trial.Using other treatment methods or drugs that are prohibited from being used in combination.Serious adverse events during the study period.Patients are unwilling to continue the trial and ask to withdraw from the trial.Poor subject compliance of patients (such as taking drugs in violation of the prescribed dose, or using prohibited drugs).Poor compliance of patients (trial medication adherence <80% or >120%).Blind release or emergency unblinding.Researchers decided to withdraw the patient from the trial.

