#### Primary outcome

2.5.1

##### Clinical symptom improvement rate on day 4

2.5.1.1

The primary outcome is early clinical response, defined as an improvement in at least two of four symptoms (cough, chest pain, sputum production, dyspnea) without any exacerbation of any symptom within 96 h following the initial dose of study medication in the intention-to-treat population (24).

An improvement in symptoms is defined as a reduction in severity by a minimum of one grading level. Refer to Table 2 for details.

**Table 2 tab2:** Community-acquired pneumonia symptom severity assessment scale.

Symptoms	Asymptomatic	Mild	Moderate	Severe
Cough	No cough	Coughing, but does not interfere with daily activities	Frequent cough that interferes with daily activity	Coughing day and night, most daily activities limited, sleep disrupted
Expectoration	No expectoration	Mild expectoration	Moderate expectoration	Excessive expectoration
Pleurisy pain	No pneumonia-related chest pain	Occasional chest pain during deep breathing, but does not interfere with daily activities	Chest pain during normal breathing, affecting daily activities	Chest pain occurs during rest or shallow breathing, and most daily activities are limited
Dyspnea	No dyspnea	Shortness of breath during intense activities, but does not interfere with daily activities	Frequent dyspnea that interferes with daily activity	Dyspnea occurs during mild activity or at rest, and most daily activities are limited

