##### Clinical cure rate

2.5.2.1

The clinical cure rate (25) is defined as the proportion of patients in each group with complete resolution of the four major clinical symptoms (cough, sputum, pleuritic chest pain, dyspnea) and no requirement for further antimicrobial therapy by day 14. The clinical cure rate will be evaluated on day 14 of enrollment.

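### Section 2.2.4 requires withdrawal from the trial after events such as serious adverse events, worsening or poor adherence, and does not separate stopping study drug from ending follow-up, so outcomes can be lost

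*Protocol article*

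**What the plan says.** Section 2.2.4 opens its list with "Patients will be required to withdraw for the following reasons". The listed reasons include:

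- "condition worsens, requiring discontinuation of the trial"
- "Serious adverse events during the study period", with no requirement that the event be related to study drug
- "Using other treatment methods or drugs that are prohibited from being used in combination"
- "Poor compliance of patients (trial medication adherence <80% or >120" (per cent)
- "Researchers decided to withdraw the patient from the trial"

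The last item shows that withdrawal here means leaving the trial. The section heading mentions management, but the printed text gives criteria only and says nothing about assessment after withdrawal.

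Other sections bear on this:

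- Section 2.5.1.1 sets the primary outcome "in the intention-to-treat population" and treats exacerbation of any of the four symptoms as non-response.
- Section 2.5.2.1: "The clinical cure rate will be evaluated on day 14 of enrollment".
- Section 2.10.2 admits a patient to the full analysis set (FAS) only with at least one dose and at least one assessment after randomisation. Its per-protocol set (PPS) already requires adherence to the protocol and no major violations.
- Section 2.8 schedules visits at enrolment and days 4, 7 and 14.

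**The concern.** The triggers occur after randomisation, and some are close to the outcome itself. Worsening is the clearest case: section 2.5.1.1 counts an exacerbation as a primary-outcome failure, while section 2.2.4 makes worsening that requires discontinuation a ground for leaving the trial. If assessment ends at that point, a failure becomes a missing value. If it happens before the first post-baseline visit, the patient may not enter the FAS at all.

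For the later outcomes (cure, CASA-Q, antibiotic course and adverse events to day 14), the rule can end follow-up in patients whose results may differ systematically from the rest. If the arms differ in how often this happens, the comparison is biased. An analysis plan can impute such values, but it cannot recover visits that were never made.

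**Working it through.** **The plan's own figures.** Inputs from section 2.9: 78% and 92.5% response, two-sided 5%, 80% power, 1:1 allocation, about 20% dropout.

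With unpooled variance, n per arm = (1.960 + 0.842)² × (0.78 × 0.22 + 0.925 × 0.075) / 0.145² = 89.96, so 90 per arm and 180 in total. Then 90 / 0.80 = 112.5, so 113 per arm and 226. Both figures reproduce, and neither is disputed.

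**Planned loss against expected failures.** 226 − 180 = 46, or 23 per arm. Expected failures among 113 are 0.22 × 113 = 24.9 (control) and 0.075 × 113 = 8.5 (treatment). The allowance is therefore about as large as all expected control failures and larger than all expected treatment failures. Failure-related loss could matter without exceeding it.

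**When each trigger acts.** Worsening, serious adverse events and prohibited treatment can occur before day 4 and so can affect the primary outcome. Adherence is measured over 7 × 3 = 21 bags; 0.80 × 21 = 16.8 and 1.20 × 21 = 25.2. It is fully known only at about day 7, when the day-4 result should already exist. A very early stopper could be identified sooner, but in the main this trigger puts day-14 data at risk.

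**Effect on the day-4 comparison (assumed withdrawal fractions).** Suppose no true effect, with response p = 0.78 in both arms. A fraction f of failures leaves unobserved, and only observed patients are compared. Observed rate = p / (1 − f(1 − p)). Rejection is for a two-sided 5% normal-approximation test starting from 113 per arm.

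| Failures lost, control / treated | Loss in arm | Observed, control / treated | Difference | Rejection |
|---|---|---|---|---|
| 25% / 50% | 5.5% / 11% | 82.5% / 87.6% | +5.1 points | about 17% |
| 25% / 75% | 5.5% / 16.5% | 82.5% / 93.4% | +10.9 points | about 65% |
| 50% / 25% | 11% / 5.5% | 87.6% / 82.5% | −5.1 points | about 17% |

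For the first row: 0.78 / (1 − 0.25 × 0.22) = 0.78 / 0.945 = 0.825 and 0.78 / (1 − 0.50 × 0.22) = 0.78 / 0.89 = 0.876. All these losses lie inside the 20% allowance.

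**If withdrawn patients are scored as non-responders.** Take completers responding at 78% and 92.5%, with the same withdrawal fraction w in both arms, so rates become 0.78(1 − w) and 0.925(1 − w) with 113 per arm. Power is about 75%, 64%, 55% and 46% at w = 5%, 10%, 15% and 20%. Analysing completers alone would give 86%, 84%, 81% and 79%. Such scoring keeps every patient in the analysis, but at a cost in power.

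**The case against.** The strongest reply is that section 2.2.4 never says assessments stop. What happens after withdrawal is detail that a journal article commonly leaves to the full protocol. Section 2.10.5 counts both dropouts and patients who end treatment early among the 114 at the interim look, so the article does not wholly ignore the distinction. An intention-to-treat analysis can also include withdrawn patients under a scoring rule, which may be in an analysis plan not shown here.

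Much of this stands, and it rules out several stronger readings:

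- **That outcomes are known to be lost.** This is an inference from mandatory withdrawal from the trial; the text does not state it.
- **That the intention-to-treat wording is flatly contradicted.** It is at odds with the rule only if data collection ends or the patient falls out of the FAS.
- **That every trigger marks treatment failure.** Worsening is qualified by the need to discontinue, a serious adverse event may be unrelated, and adherence outside 80–120% is not failure. A patient withdrawn for adherence at about day 7 would normally stay in the FAS with a day-4 result.
- **That the bias favours the granules, or that the 20% allowance stems from these rules.** The article gives no withdrawal rates by reason or by arm, and the allowance is not broken down by cause.

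The reply does not remove the rule itself. It is stated, mandatory and phrased as leaving the trial. Section 2.10.5 does not say how early terminations are scored or whether they are still seen at days 7 and 14.

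**Conclusion.** The point holds as a weakness in a stated rule, not as demonstrated loss of data. Followed as written, section 2.2.4 can remove day-4 failures through worsening or serious adverse events, and day-14 data through the adherence trigger. For adherence it gains nothing, because the PPS already excludes non-adherent patients.

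The size and direction of bias cannot be determined from the document. The range of about +5 to +11 points, reversible in sign, rests on assumed loss fractions, no true effect and an analysis of observed patients only. The article does not specify that last choice. It shows that losses within the planned allowance could matter against an assumed effect of 14.5 points (92.5 − 78). This should be corrected, since amendment is cheap and, per section 2.2.1, enrolment runs to December 2027.

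**What to change.** In section 2.2.4, separate two states: *study drug discontinued*, and *withdrawn from study*, the latter limited to withdrawn consent or loss to follow-up. State that all other randomised patients are still assessed at days 4, 7 and 14 and for adverse events, whether or not they are on drug. Use the 80–120% adherence threshold to define the PPS in section 2.10.2, not to end follow-up. Which events stop study drug is a clinical matter and is not changed here.

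The cost is a short amendment with a note to the 11 sites, and some effort to follow patients who are off drug; the visits are already scheduled and 226 stands. Recruitment began in January 2023, so outcomes of any patients already withdrawn and not followed under the present rule cannot be recovered. Patients handled before and after the amendment will have been under different rules, which the report should state.

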### Allocation and blinding

2.3

A central Interactive Web Response System (IWRS) will assign unique treatment codes for each patient, as well as bottle numbers and instructions for dispensing the blinded study drug that matches the assigned treatment. This study will use the Electronic Data Capture System (EDC) (Copyright^©^ 2012–2023 Clt. Inc. V1.0) to collect research data, which is managed by the Clinical Trial Service (Guangzhou) Co., Ltd. According to the research plan, an electronic Case Report Form (eCRF) will be designed and an EDC database will be established. The database complies with China’s Good Clinical Practice (GCP) guidelines. We will use stratified randomization, with age as the stratification factor. Each center will compete for enrollment, and eligible cases will be allocated to the YMJD granules treatment group or YMJD placebo control group in a 1:1 ratio through the central random allocation system.

This double-blind trial maintains blinding integrity through independent unblinded personnel according to the double-blind trial standards and procedures to ensure the blind status of the trial group by the sponsor, researcher, relevant researchers, and patients. The unblinded personnel will include pharmacists responsible for the preparation and dispensing of the investigational drug and placebo, an independent statistician who will generate the randomization sequence and manage blinding code documents, and a monitor external to the research team who will conduct periodic audits of drug distribution records and blinding compliance to ensure protocol adherence. Following trial completion, patients and investigators will complete a blinding assessment questionnaire to guess group allocation (intervention or placebo).

The study employs a central system for emergency unblinding without paper correspondence. Unblinding is reserved for urgent medical needs or regulatory requests. Before unblinding, the sponsor must be notified, and the principal investigator will execute the process, noting the reasons. The unblinding details and any adverse events are meticulously recorded.

### Interventions

2.4

After being recruited, patients will be stratified by age and then randomly allocated to either the intervention group or the control group (in a 1:1 ratio). Both groups can be treated with conventional Western medicine, according to the “Guideline of Diagnosis and Treatment for Community-Acquired Pneumonia among Adults in China (released in 2016) (20),” which sets the following criteria for routine use of antimicrobial drugs in hospitalized CAP patients: intravenous cephalosporin; intravenous cephalosporin combined with macrolides; intravenous quinolones. In addition, oxygen therapy, antipyretics, and rehydration support are used as needed. Based on the treatment of conventional Western medicine, patients will receive YMJD granules or YMJD placebo three times per day for 7 days, taking one bag after each meal. The YMJD placebo is consistent with YMJD granules in terms of packaging, appearance, odor, and taste, the composition is shown in Table 1. The drug quality standard complies with the provision of the Chinese Pharmacopoeia and GMP.

**Table 1 tab1:** Drug composition.

Drug	Specifications	Producer	Composition
Yinma Jiedu granules	10 g/bag	Yangtze River Pharmaceutical Group Sichuan Hairong Pharmaceutical Co., Ltd., China	Honeysuckle flower, purslane herb, plantain herb, rhubarb root and rhizome, and licorice root
Yinma Jiedu placebo	10 g/bag	Yangtze River Pharmaceutical Group Sichuan Hairong Pharmaceutical Co., Ltd., China	Dextrin, caramel coloring, fructokinin, sucrose octaacetate, sucralose, PVP K30, DL-Tartaric acid, hawthorn flavor, pickled plum, flavoring, anhydrous ethanol and purified water

Except for the experimental drugs, patients are not permitted to use any therapeutic agents that may affect the determination of efficacy, such as cough suppressants and phlegm reducers, glucocorticoids. In addition, the utilization of Chinese patent medicines, Chinese medicines, Chinese medicine granules, or TCM characteristic therapy aimed at clearing heat, resolving phlegm and relieving cough are also prohibited during the trial. If any other medication or therapy is required to treat concomitant diseases, the name of the drug or therapy, actual dosage, dosing frequency, and start/stop time will be well-documented.

### Outcomes

2.5

#### Primary outcome

2.5.1

##### Clinical symptom improvement rate on day 4

2.5.1.1

The primary outcome is early clinical response, defined as an improvement in at least two of four symptoms (cough, chest pain, sputum production, dyspnea) without any exacerbation of any symptom within 96 h following the initial dose of study medication in the intention-to-treat population (24).

An improvement in symptoms is defined as a reduction in severity by a minimum of one grading level. Refer to Table 2 for details.

**Table 2 tab2:** Community-acquired pneumonia symptom severity assessment scale.

Symptoms	Asymptomatic	Mild	Moderate	Severe
Cough	No cough	Coughing, but does not interfere with daily activities	Frequent cough that interferes with daily activity	Coughing day and night, most daily activities limited, sleep disrupted
Expectoration	No expectoration	Mild expectoration	Moderate expectoration	Excessive expectoration
Pleurisy pain	No pneumonia-related chest pain	Occasional chest pain during deep breathing, but does not interfere with daily activities	Chest pain during normal breathing, affecting daily activities	Chest pain occurs during rest or shallow breathing, and most daily activities are limited
Dyspnea	No dyspnea	Shortness of breath during intense activities, but does not interfere with daily activities	Frequent dyspnea that interferes with daily activity	Dyspnea occurs during mild activity or at rest, and most daily activities are limited

#### Secondary outcomes

2.5.2

##### Clinical cure rate

2.5.2.1

The clinical cure rate (25) is defined as the proportion of patients in each group with complete resolution of the four major clinical symptoms (cough, sputum, pleuritic chest pain, dyspnea) and no requirement for further antimicrobial therapy by day 14. The clinical cure rate will be evaluated on day 14 of enrollment.

##### Improvement rate of single symptoms (including cough, expectoration, pleurisy chest pain, and dyspnea)

2.5.2.2

Assess the variations in single clinical symptoms (including cough, expectoration, pleurisy chest pain, and dyspnea) of the patients in the two groups before and after treatment. Symptoms severity is classified into four levels, including asymptomatic, mild, moderate, and severe. Symptom improvement is defined as a decrease in severity by at least one level (e.g., from moderate to mild). The improvement rate of single symptoms will be evaluated on day 1, day 7, and day 14 of enrollment.

##### Cough and Sputum Assessment Questionnaire (CASA-Q)

2.5.2.3

Assess the changes in cough and sputum symptoms of two groups of patients before and after treatment using the CASA-Q questionnaire (26). The CASA-Q questionnaire will be conducted on day 1, day 7, and day 14 of enrollment.

##### Pneumonia Imaging Absorption Evaluation Scale

2.5.2.4

Patients record pneumonia uptake by Pneumonia Chest X-ray Absorption Evaluation Scale on day 1 and day 7 of enrollment (27). Two imaging experts will independently evaluate the scores of the improved version of the Modified Pneumonia Imaging Absorption Evaluation Scale, and then take the average value.

##### CURB-65 score

2.5.2.5

Patients will be assessed for severity of illness and risk of mortality by the CURB-65 score on day 1 and day 7 of enrollment (28), including state of consciousness, blood urea nitrogen value, respiratory rate, blood pressure, and age. An elevated total score indicates a graver condition.

##### Dosage and course of antibiotics

2.5.2.6

To assess the total dosage and duration of medication administered from enrollment to the end of follow-up for patients in both groups treated with three anti-infective regimens: cephalosporins, cephalosporins combined with macrolides, and respiratory quinolones. Anti-infective therapy may be discontinued if clinical symptoms improve significantly, including vital signs, eating ability, and psychological state, Continuous treatment time not less than 5 days (11, 20).

##### Changes in inflammatory indicators

2.5.2.7

Evaluate the improvement of systemic infection indicators in two groups of patients on day 1 and day 7 of enrollment, including C-reactive protein, serum procalcitonin, interleukin 6, serum amyloid A.

##### TCM syndrome points

2.5.2.8

Total TCM syndrome scores and individual symptom scores (cough, expectoration, pleusity pain, and dyspnea) will be assessed on day 1, day 4, day 7 and day 14 of enrollment. Detailed evaluation criteria are summarized in Table 3 (29). TCM syndromes were independently assessed by two physicians, if there were any discrepancies in the determination of TCM syndrome patterns, a third physician would adjudicate the case to ensure the accuracy of syndrome differentiation and minimize bias.

**Table 3 tab3:** TCM syndrome points.

Main symptom points	Score			
Fever	□ None (0)	□ Mild (3)	□ Moderate (6)	□ Severe (9)
Cough	□ None (0)	□ Mild (3)	□ Moderate (6)	□ Severe (9)

Secondary symptom points	Score	
Chest and hypochondriac fullness causing pain during coughing	□ No (0)	□ Yes (1)
Yellowish white sputum	□ No (0)	□ Yes (1)
Sweating	□ No (0)	□ Yes (1)
Desire to drink water	□ No (0)	□ Yes (1)
Red face	□ No (0)	□ Yes (1)
Insufficient appetite	□ No (0)	□ Yes (1)
Yellow urine color	□ No (0)	□ Yes (1)
Dry stool	□ No (0)	□ Yes (1)
Abnormal respiratory sounds in the lungs	□ No (0)	□ Yes (1)
Total score	_________	

##### Improvement rate of TCM evidence of efficacy

2.5.2.9

Improvement rate of TCM syndrome efficacy on day 4, day 7, and day 14 of enrollment. Referring to the criteria for determining the efficacy of the symptoms in the relevant literature, the treatment results were classified into four levels: clinically cured, apparently effective, effective and ineffective (29).
$$\begin{array}{l} \text{Improvement rate of Chinese medical evidence efficacy}=\\ (\begin{array}{l} \text{number of cured cases}+\text{number of apparently}\;\\ \text{effective cases}+\text{number of effective cases}+\\ \text{number of ineffective cases} \end{array})/\\ \text{total number of cases}\times 100\% \end{array}$$

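### The formula for the TCM efficacy improvement rate counts ineffective cases as improved, so every classified patient is a success and the rate is 100% in both arms

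*Protocol article*

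**What the plan says.** Section 2.5.2.9 of the protocol article, listed under the secondary outcomes, schedules the "Improvement rate of TCM syndrome efficacy on day 4, day 7, and day 14 of enrollment". It says that "the treatment results were classified into four levels: clinically cured, apparently effective, effective and ineffective".

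The formula that follows has four terms inside the numerator bracket, joined by plus signs: the "number of cured cases", the apparently effective cases, the "number of effective cases" and the "number of ineffective cases". The divisor is the "total number of cases", and the result is multiplied by 100%.

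Table 4 repeats the three visits. Section 2.10.3 (Analysis method) plans, for categorical data, a CMH comparison of the arms and a stratified Newcombe interval for the rate difference. No other part of the article gives a different formula for this outcome.

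**The concern.** An improvement rate should count patients who improved, over all patients. Here the one level that denotes failure is also counted as success. Because the levels are exhaustive and do not overlap, adding the fourth turns the numerator into a count of everyone classified, and nothing is left that treatment could change.

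At stake is a scheduled efficacy outcome at three visits. An analysis that follows the text would report identical rates in both arms, which could be misread as evidence of no effect on TCM syndrome. An analysis that silently departs from the text would use a definition other than the published one.

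**Working it through.** **Inputs**

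- Numbers of patients who are cured (a), apparently effective (b), effective (c) and ineffective (d), and the divisor N: section 2.5.2.9.
- 113 patients per arm, used only for illustration: section 2.9.
- CMH and Newcombe methods: section 2.10.3.

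The article states no expected value for this outcome, so there is no figure to reproduce.

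**1. The formula as printed**

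Rate = (a + b + c + d) / N × 100%.

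Each classified patient is in exactly one level, so a + b + c + d = N and the rate is N / N = 100%. As a check, all 253,460 ways of dividing 113 patients among four levels were enumerated. Every one gives exactly 100%.

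**2. Effect on the planned analysis**

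- Rate difference: 100% − 100% = 0.
- CMH: its variance in each stratum is proportional to (successes × failures). With no failures the variance is 0 and the statistic is 0/0, that is, undefined.
- Newcombe interval: for 113/113 against 113/113, the unstratified 95% interval is about −3.3 to +3.3 percentage points. Its width depends only on the number of patients and carries no information about treatment.

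**3. The formula without the ineffective term**

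Rate = (a + b + c) / N = 1 − d / N. This can take any value from 0% to 100% and can differ between arms.

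The counts below are assumed for illustration and are not forecasts:

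| | Treatment (N = 113) | Control (N = 113) | Difference |
|---|---|---|---|
| Ineffective (d) | 10 | 25 | |
| Printed formula | (103 + 10)/113 = 100% | (88 + 25)/113 = 100% | 0 |
| Without d in the numerator | 103/113 = 91.2% | 88/113 = 77.9% | 15/113 = 13.3 points |

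**4. If N also counts patients with no assessment at the visit**

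The numerator is then the number assessed, and the printed ratio is the proportion assessed:

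- 11 of 113 missing: 102/113 = 90.3%.
- 23 of 113 missing (close to the 20% dropout assumed in section 2.9): 90/113 = 79.6%.

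The ratio is no longer 100%, but it still says nothing about improvement. A difference between arms would reflect missing data alone.

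**The case against.** The algebra is not open to dispute: the formula is printed whole, with a plus sign before the last term. The case on the other side concerns weight.

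- **It looks like a drafting slip with an obvious meaning.** The name of the outcome and of its lowest level make the intention plain, and 100% in every arm would show at the first test run of the programs. That is likely true. It makes the slip easy to catch, but the published definition of a prespecified outcome is still wrong.
- **Little is lost.** This is one of ten secondary outcomes. The four-level grading is still recorded for each patient, the TCM syndrome score is a separate outcome (section 2.5.2.8), and the correct rate can be computed at any time. This stands: the outcome is uninformative as written, but the data behind it are not lost.
- **The rate need not be exactly 100%.** The article does not say whom the divisor counts. The full analysis set (section 2.10.2) requires only one post-randomization assessment, so some of its patients may have no day 7 or day 14 grade. This also stands as a qualification. The 100% result and the undefined CMH statistic hold when the divisor is the classified patients; otherwise the ratio measures completeness. Neither reading measures improvement.
- **The full protocol or the SAP may be correct.** Neither is shown, and the slip may have entered when the article was condensed. In that case the article contradicts them and still needs correcting. The definition was not left to another document: it was stated, and stated wrongly.

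**Conclusion.** The concern holds. Among classified patients the printed formula gives 100% in each arm at days 4, 7 and 14, whatever the treatment effect. This rests only on the four levels being exhaustive and mutually exclusive, as section 2.5.2.9 presents them. If unassessed patients are in the divisor, the formula returns the proportion assessed, which is equally useless as a measure of efficacy.

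The damage is confined to this one secondary outcome at its three visits. The primary outcome, the sample size and the TCM syndrome score are unaffected. Within that limit the failure is total: the formula cannot show a difference in efficacy of any size. It must be corrected.

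**What to change.** Delete the ineffective term from the numerator, so that the rate is (cured + apparently effective + effective) / total cases × 100%. In the same sentence, say which patients the total counts and how a patient with no grade at a visit is handled. The arms can then be compared with the age-stratified CMH test and stratified Newcombe interval already planned.

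Check the full protocol, the SAP and the programming specification for the same formula, and correct it wherever it recurs. Date the correction, preferably before the unblinded interim analysis at 114 patients (section 2.10.5), so that it is plainly independent of the results.

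The cost is a one-line change to the text. No new data, visits or patients are needed.
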